### **Exploratory objective**

Explanatory outcomes include stool microbiome and Vineland 3. The similar analyses as ones for primary and secondary objectives will be carried out based on data types.

Analyses will be conducted using the programs of SAS v9.4 (SAS Institute, Cary, NC). All tests will be two-tailed and a P value less than 0.05 will be considered statistically significant. The primary outcome will be tested at the 5% significance level. Secondary, exploratory and sensitivity analyses will not be adjusted for multiplicity. Therefore, the results will be interpreted with caution and discussed with recognition of inflated family-wise type I error rate.

Descriptive statistics will be provided on all study data collected from the total cohort (N=20) from the entry to the trial to the completion of 44 weeks follow-up continuous variables will be summarized as numbers of observed and missing values, mean, standard deviation, median, minimum and maximum. Categorical variables will be described as frequencies and percentages.

Any post-hoc, exploratory analyses or deviations which were not identified in this data analysis plan but are completed to support the planned analyses will be clearly identified and the reasons documented.

### **12.3 Power**

The sample size of 20 for the study was determined primarily by feasibility rather than statistical power due to the extremely rare nature of the disease. However, the level of precision in estimation of AEs during the treatment period was computed with a given samples size of 20 using 95% confidence interval. For estimation of the binary event, the margin of the error would be 13% to 18% when the sample proportion are assumed to be 5% to 15%. For continuous outcomes, the margin of the error would be a half fold of the standard deviation in estimation of paired difference between the treatment and first observation period.

### **12.4 Database**

All study visit data will be stored using REDCap (<https://www.project-redcap.org>). Ranges and logic reviews of the data will be performed. Access to the REDCap database will be granted over a secure web connection with authentication and data logging. Data from REDCap will be extracted, cleaned and merged into a single study dataset (stored in SAS v 9.4 for 64-bit) and saved under the secured institutional network drive and used by the study statistician [name] for all data analyses.

### **12.5 Data Quality Control**

Upper and lower limits will be included in the REDCap database to flag any entries that are not within the expected range.

### **13.0 Provisions to Monitor the Data to Ensure the Safety of Subjects**

The plan for ensuring subject safety will include the following elements:

1. Clinical procedures will only be performed by properly trained personnel who are qualified by training and licensure to perform the procedures.
2. Investigator and all study personnel have completed required training regarding Human Subject Protections. All personnel will comply with all related regulations and laws.
3. Patients will be rigorously screened against inclusion/exclusion criteria to ensure that their participation is safe.
4. Adverse events and SAEs will be assessed and followed throughout study. Subjects will have contact information to enable them to contact study personnel easily and quickly.
5. Study data and information will be kept confidential and managed in accordance with requirements of Health Insurance Portability and Accountability Act of 1996 (HIPAA). All data will be stored in locked offices and not released without subject permission.
6. Subject may discontinue participation at any time, for any reason. Any subject who fails to complete the research procedures within acceptable parameters, or is unable to safely tolerate participation in the study will be withdrawn.
7. Institutional Review Board approval and IND approval will be obtained.
8. Monitoring will be conducted by the research team, institutional review board (IRB) and independently (i.e. at a minimum of annually) by qualified staff of Harbor-UCLA Clinical and Translational Science Institute (CTSI) in accordance with the established Monitoring Plan.
9. The PI will allocate adequate time for such monitoring activities and will ensure that the monitor or other compliance or quality assurance reviewer is given access to all study-related documents and study related facilities (e.g. pharmacy, diagnostic laboratory, etc.) and has adequate space to conduct the monitoring visit.

#### **13.1 Additional Provisions to Monitor Genetic Data**

Genetic studies have raised concern as to whether the studies would place research subjects at risk for discrimination based on genetics. The federal Genetic Information Nondiscrimination Act (GINA) was passed to address this concern. GINA makes it illegal for medical insurance companies and most employers to discriminate based on genetic information. The protections of GINA do not apply to life, disability, or long-term-care insurance.

To make the best possible use of GWAS and data from large-scale genomics technologies such as sequencing, methylation and expression, the National Institutes of Health (NIH) policy requires researchers to share the information from GWAS studies with other researchers. When we perform a GWAS or other high throughput genotyping and sequencing, the data will be shared for research purposes through the NIH Genome-Wide Association Study database at the National Center for Biotechnology Information (NCBI), part of the National Library of Medicine. This is a national health research database that allows broad sharing of data to qualified investigators. All qualified investigators are required to obtain authorization from NIH to gain access to this database. All information that is shared, will be identified by a code number, and all other identification will be removed.

Once submitted, the NIH will control these data. The NIH is committed to protecting the confidentiality of all the information it receives, but will also comply with relevant laws that might include Freedom of Information Act (FOIA) requests for non-identifiable information.

However, there has been some concern that there may still be ways that research subjects' privacy might be at risk. As a result, the NIH has made access to the shared information more restricted to assure that privacy is protected. Researchers who wish to use information from this database must request access and explain how and for what purpose they will use the information. Researchers and the administration at their institution must promise to protect confidentiality and only use the information for the purposes included in the request form. They must also provide assurances that data security measures are in place to prevent misuse of the information. The NIH has security measures in place to secure all data submitted to the repository, however security breaks are possible since data is stored in an electronic format. The NIH may make more changes in the future with their data access policy.

### ***13.2 Definitions for recording/reporting adverse events***

### *Adverse Event*

An AE is any symptom, sign, illness or experience that develops or worsens in severity during the course of the study. Intercurrent illnesses or injuries will be regarded as AEs. Abnormal results of laboratory or diagnostic procedures are considered to be AEs if the abnormality:

- ☐ Results in study withdrawal
- ☐ Is associated with a serious adverse event (SAE)
- ☐ Is associated with clinical signs or symptoms
- ☐ Leads to additional treatment or to further diagnostic tests
- ☐ Is considered by the Investigator to be of clinical significance

### *Adverse Reaction*

An adverse reaction is any AE caused by a drug. Adverse reactions are a subset of suspected adverse reactions.

### *Suspected Adverse Reaction*

A suspected adverse reaction is an AE for which there is a reasonable possibility that the drug caused the AE.

### *Serious Adverse Event (SAE)*

An SAE is any AE that is:

- ☐ Fatal
- ☐ Life-threatening
- ☐ Requires or prolongs a hospital stay
- ☐ Results in persistent or significant disability or incapacity
- ☐ A congenital anomaly or birth defect

Important medical events are events that may not be immediately life-threatening, but are clearly of major clinical significance and may be SAEs. They may jeopardize the subject, and may require intervention to prevent one or the other serious outcomes noted above.

*Hospitalization*

Hospitalization shall include any initial admission (even if less than 24 hours) to a healthcare facility as a result of a precipitating clinical adverse effect; to include transfer within the hospital to an intensive care unit. Hospitalization or prolongation of hospitalization in the absence of a precipitating, clinical adverse effect (e.g. for a preexisting condition not associated with a new adverse effect or with a worsening of the preexisting condition; admission for a protocol-specified procedure) is not, in itself, a serious adverse effect.

*Expected Adverse Event*

Expected AEs are those that are known to be associated with or have the potential to arise as a consequence of participation in the study. This will include any AE or SAE that are expected consequences of having MPS . These expected events include but are not limited to, injection site reactions, injection site pain, headache, seizures, symptoms of movement disorder, sinusitis/ear infections, upper respiratory infection, fevers, nausea, vomiting, diarrhea, skin rash, pain, cardiac valve insufficiency, obstructive sleep apnea, kyphoscoliosis, genu valgum, cervical cord compression, hearing loss, in-toeing, osteonecrosis of the femoral head, retinitis pigmentosa with vision impairment, carpal tunnel syndrome, and trigger fingers.

*Unexpected Adverse Event*

An AE or suspected adverse reaction is considered unexpected if it is not listed in the drug package insert or Protocol at the specificity or severity that has been observed.

*Unanticipated Problems Involving Risk To Subjects or Others (UPIRTSO)*

An AE that in the opinion of the PI is unexpected, related to the drug, and serious.

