### **FDA Notification by Sponsor**

The study Sponsor shall notify the FDA by telephone or by fax (preferred) transmission of any unexpected SAE associated with the use of the study drug for which the Investigator holds an active IND as soon as possible but no later than 7 calendar days from the Sponsor's original receipt of the information.

If a previous AE that was not initially deemed reportable is later found to fit the criteria for reporting, the study Sponsor will submit the AE in a written report to the FDA (as applicable) as soon as possible, but no later than 15 calendar days from the time the determination is made.

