### **15.2 Anakinra**

The following have been reported as adverse reactions related to anakinra in other studies:

- Serious infections (e.g. Cellulitis, pneumonia, sinusitis, upper respiratory tract infections, ear infections, nasopharyngitis, gastritis, bone and joint infections, from fungal, mycobacterial and bacterial pathogens)
- Injection-site reactions (e.g. Erythema, ecchymosis, inflammation, and pain)
- Malignancies (e.g. Lymphomas, breast, respiratory, and digestive system cancers)
- Hematologic events (e.g. Decreased total white blood cell counts, neutropenia, eosinophilia, thrombocytopenia, epistaxis)
- Hypersensitivity reactions including anaphylactic reactions, angioedema, urticaria, rash, and pruritis
- Immunogenicity (i.e. Anti-anakinra binding antibodies)
- Headache, dizziness
- Nausea, diarrhea, abdominal pain
- Arthralgia
- Flu-like symptoms; pyrexia, malaise

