**Serious Adverse Event and Unexpected Adverse Events:**

- ☒ For all study-related serious adverse events (SAEs) and study-related unexpected adverse events (UAEs), the clinical summary will also be provided in a cumulative fashion.
- ☒ Due to the large number of disease-related SAEs such as  Hospitalization and/or surgery due to seizure, vomiting/diarrhea/dehydration, cervical cord compression, or osteonecrosis of the femoral head. New onset or worsening of visual impairment.  
these serious adverse events will be tracked and evaluated by treatment group at each DSM periodic reporting but will not be reported by expedited reporting to the IRB.
- ☐ For all serious adverse events (SAEs) and all unexpected adverse events (UAEs), the clinical summary will also be provided in a cumulative fashion.

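### Section 13.2 lets an MPS III disease listing make a drug-related serious seizure or movement-disorder event expected, so it can miss both expedited reports

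*Protocol*

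**What the plan says.** Protocol section 13.2 has one category of expected adverse event. It holds events that may follow from taking part in the study and adds disease events: "This will include any AE or SAE that are expected consequences of having MPS". The list is open-ended ("These expected events include but are not limited to") and includes "headache, seizures, symptoms of movement disorder, sinusitis/ear infections", with no type, grade or severity for the seizures or movement symptoms.

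The same section calls an event unexpected if it is "not listed in the drug package insert or Protocol at the specificity or severity that has been observed". A UPIRTSO is an event that the investigator considers unexpected, drug-related and serious, all three together.

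Section 13.5 uses that word for both outside routes. The sponsor notifies the FDA within 7 calendar days of "any unexpected SAE associated with the use of the study drug". The IRB receives SAE reports within 10 working days if they meet the UPIRTSO criteria. Deaths go to the IRB whatever their cause or expectedness.

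Section 15.2 lists adverse reactions reported with anakinra in other studies. Seizures and movement disorder are not among them.

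Appendix A, item 2, says that certain disease-related SAEs, among them hospitalization due to seizure, will be tracked in the periodic report "but will not be reported by expedited reporting to the IRB".

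**The concern.** Whether an event is expected from the disease and whether it is expected from the drug are different questions. The first helps in reading a background rate. The second decides whether a drug-related event tells regulators and the IRB something new. Section 13.2 answers both with one list. Because a listing in the Protocol is enough, a disease term can settle the drug question as well.

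This matters most for seizures and movement disorder. Safety is the first primary objective (section 3.0). Caregivers record seizures in real time (10.12), and the analysis section gives the total number of seizures as an example of an event count tested between periods (12.2). Movement disorder is a component of the MDRI (9.1). The effect of anakinra on either in MPS III is what the trial sets out to learn. A serious worsening attributed to the drug is the kind of event on which the FDA and IRB would want prompt word, and both may terminate the study under 13.4.

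**Working it through.** No arithmetic applies. The check follows a serious event, judged related under section 13.3, through the reporting rules.

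**Step 1: is it expected?** Both terms stand in the 13.2 list, so on a plain reading they are listed in the Protocol. The definition of unexpected does not ask why a term is listed (drug or disease) and does not mention relatedness. The only way out is the qualifier on specificity or severity. With bare terms, and with SAEs expressly included among the disease events, the text gives no level above which an event stops being covered.

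**Step 2: which routes depend on the answer?**
- FDA notice, 13.5: requires unexpected, serious and associated with the drug.
- UPIRTSO/IRB report, 13.2 and 13.5: requires unexpected, serious and related.
- SAE report to the sponsor, 13.5: every SAE within 24 hours, with a narrative in the following 48 hours and no expectedness test.
- Death report to the IRB, 13.5: no expectedness test.
- Periodic report to the independent monitor, Appendix A: every 6 months, with a summary of study-related SAEs.

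**Step 3: trace four cases, all judged related.**

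| Event | Expectedness under 13.2 | 7-day FDA notice | 10-working-day IRB report |
|---|---|---|---|
| Non-fatal serious seizure, no more specific or severe than the listed term | Can be classed expected | Can be missed | Can be missed; Appendix A also points away from it if the child is hospitalized |
| Non-fatal serious movement-disorder worsening within the listed term | Can be classed expected | Can be missed | Can be missed; Appendix A does not name this event |
| Either event, more specific or severe than listed | Can be classed unexpected | Due if so classed | Due if so classed |
| Fatal event | Depends on classification | Depends on classification | Always due |

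The gap is in the first two rows.

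**Step 4: would a drug-only reference change the result?** Against section 15.2, neither term is listed, so rows one and two would become unexpected and reach both routes. The package insert is not part of the documents. This step assumes that it does not list seizures or movement disorder either. If it does list one of them, that event would stay expected under the corrected rule too, and properly so.

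**Step 5: Appendix A against 13.5.** Section 13.5 sends an SAE to the IRB when it is unexpected and related. Appendix A withholds named SAEs from expedited IRB reporting because they are disease-related. It does not say which rule governs when such an event is judged related to anakinra.

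**The case against.** The strongest reply has four parts.

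First, the specificity and severity qualifier in 13.2 means that a bare term does not cover every seizure. A reader might infer that a related seizure could never be unexpected. The text does not support that, and a more severe or more specific event can be classed unexpected. What remains is that no threshold is stated, so the outcome rests on judgment.

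Second, a seizure judged related to the drug is arguably no longer a consequence of having MPS. That reading is open, but 13.2 does not state it. The definition of unexpected asks only whether the event is listed.

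Third, such events do not disappear. Every SAE reaches the sponsor within 24 hours, and deaths always reach the IRB. One Grade 4 event, or two patients with the same Grade 3 event, is a listed reason for terminating the study regardless of expectedness (13.4). An event later found to meet the criteria goes to the FDA within 15 calendar days. All AEs are recorded for analysis. It would therefore be wrong to infer that a related event lies unseen until the 6-monthly report, or that the primary safety data are damaged. These routes do not close the gap, however. The contents page puts investigator and sponsor under one heading, so the 24-hour report may add little independent review, and the 15-day rule uses the same criteria.

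Fourth, the Appendix A exemption is worded for disease-related events, and the appendix keeps the investigator's duty to report what may be an unanticipated problem. The intended limit may be implicit, but it is not stated.

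Two further inferences should be resisted. Counting how many terms in the 13.2 list are missing from 15.2 does not measure the gap: the rule refers to the package insert, which is not available here, and a count of terms says nothing about how often events occur. Nor does the exemption for vomiting and diarrhea illustrate a hidden signal. Section 15.2 lists "Nausea, diarrhea, abdominal pain" as anakinra reactions, so diarrhea would stay expected under a drug-only test.

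**Conclusion.** The concern holds in a limited form. As written, 13.2 permits a non-fatal SAE judged related to anakinra to be classed as expected because the Protocol lists it as a disease event, and so to miss both the 7-day FDA notice and the 10-working-day IRB report. It applies to events no more specific or severe than the listed term. Seizures and movement-disorder worsening are the cases that matter, because 15.2 names neither and the trial evaluates both. Appendix A adds to the gap for hospitalization due to seizure, on the IRB side only.

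The documents do not allow an estimate of how many events would be affected among the 20 subjects. The conclusion rests on a plain reading of the definition of unexpected and, for the effect of the correction, on the package insert listing neither event. The rule should be corrected, because it bears on timely outside review of a possible drug effect and the correction is simple.

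**What to change.** Three wording changes:

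1. In 13.2, state that for any SAE judged related to study drug, expectedness is assessed only against drug reference information, namely the package insert and the anakinra reactions in section 15.2. Striking the reference to the Protocol outright would be too blunt, since 15.2 is itself part of the Protocol.
2. Keep the MPS III terms as a separate list of anticipated disease events, used for periodic tabulation of events judged unrelated.
3. In Appendix A, limit the exemption from expedited IRB reporting to listed SAEs judged not related to study drug, so that it agrees with 13.5.

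The cost is an amendment to 13.2 and Appendix A and possibly a few more expedited reports among 20 subjects. Dosing, design, data collection and analysis are unchanged.

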**13.3 Recording of Adverse Events**

At each contact with the subject, the Investigator must seek information on AEs by specific questioning and, as appropriate, by examination. Information on all AEs should be recorded immediately in the source document, and also in the appropriate AE module of the case report form (CRF). All clearly related signs, symptoms, and abnormal diagnostic procedures results should be recorded in the source document, though should be grouped under 1 diagnosis.

All AEs occurring during the study period must be recorded. The clinical course of each event should be followed until resolution, stabilization, or until it has been determined that the study treatment or participation is not the cause. Serious adverse events that are still

ongoing at the end of the study period must be followed up to determine the final outcome. Any SAE that occurs after the study period and is considered to be possibly related to the study treatment or study participation should be recorded and reported immediately.

Toxicity and AEs will be classified according to the National Cancer Institute (NCI) Common Toxicity Criteria (CTC) V 4.1 and causality will be classified as:

Unrelated - The AE is likely NOT related to study treatment or procedures

Related - The AE is likely related to study treatment or procedures

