## 9.0 Study Endpoints

### 9.1 Primary and secondary endpoints.

#### Primary endpoints:

Phase 1: Incidence of treatment-emergent adverse events and laboratory values over 8 weeks of treatment to known frequency of anakinra-related AEs in other populations.

Phase 2: Need for dose escalation as determined by within individual change over 8-week treatment period compared to change over 8-week observational period in the 2 most bothersome symptoms for each enrolled patient, selected from measures for the MDRI. Choices are below in bold. These 2 symptoms will be monitored by one or more of the assessments below. If the Minimal Clinically Important Difference (MCID) that is defined below is not achieved after 8 weeks of treatment, or there has been a decrease of more than the MCID between 8 and 16 weeks after an increase greater than MCID at week 8, the dose will be escalated (see Section 27.7). If the MCID is not achieved after 8 weeks on maximum trial dose of 200mg (max dose 8 mg/kg/day), treatment with anakinra may be discontinued (see Section 27.7).

- Sanfilippo **Behavior** Rating Scale (SBRS): MCID = 0.25 SD for each scale
  - Symptoms described in table below:

|                         |                                                                                                                                        |                           |
|-------------------------|----------------------------------------------------------------------------------------------------------------------------------------|---------------------------|
| Body Movements          | Makes large complex movements of their body, such as spinning, twirling or repeatedly bouncing up and down.                            | Movement                  |
| Object Interaction      | Examines or manipulates some novel or unfamiliar objects repeatedly.                                                                   |                           |
| Activity/Routines       | Never plays with one object or engages in one activity for very long.                                                                  |                           |
| Emotional Function      | Expresses emotions inappropriate to the situation.                                                                                     | Social/emotional function |

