### ***10.19 Lumbar puncture and CSF collection***

**CSF collection will be limited to participants for whom the procedure can be conducted using only mild sedation (one agent, responds to voice; e.g. oral midazolam or lorazepam only) and without use of ultrasound or fluoroscopy.**

In addition, **parents/guardians may opt out of CSF collection** even if their child meets the above criteria due to parental concerns, e.g. potential amplified negative impact of repeated sedation on the brain of their children specific to having a neurometabolic disease.

For those meeting the criteria above and whose parents/guardians consent to CSF collection, CSF will be collected at Day 1, Week 36, and Week 44 for inflammatory (IL-1 $\beta$ , TNF- $\alpha$ ) and GAG (heparan sulfate non-reducing ends I0S0 and I0S6) biomarkers.

CSF will be collected using the following procedures:

1. The subject will be taken to a procedure room where equipment and medications necessary for resuscitation will be in the room. A local anesthetic (lidocaine dose as appropriate) will be administered in the skin and underlying tissue above the chosen interspace. A small spinal needle will be inserted under sterile conditions into the lumbar spinal sac. A small amount of CSF (roughly 5-8 mL) will be collected for biomarker evaluations.
2. Family members will be provided clear instructions regarding the post discharge monitoring of the subject for anticipated adverse events (AE).

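### Section 13.3 codes causality on one two-level scale that merges drug with procedures and conflicts with the drug-only standard in 13.2, so it cannot supply the drug-attributed events needed for the benchmark in 9.1

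*Protocol*

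**What the plan says.** Section 13.3 allows two causality codes: "Unrelated - The AE is likely NOT related to study treatment or procedures" and "Related - The AE is likely related to study treatment or procedures". The protocol defines no other causality scale. The same section uses a different standard, a possible relation to treatment or participation, for SAEs that arise after the study period.

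Section 13.2 sets its own threshold: "A suspected adverse reaction is an AE for which there is a reasonable possibility that the drug caused the AE". Its UPIRTSO definition is also drug-specific: "An AE that in the opinion of the PI is unexpected, related to the drug, and serious". In 13.5, the IRB and FDA triggers refer to the study drug, and the initial SAE report must include the investigator's view of the link with study treatment.

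Appendix A selects, for the periodic report to the Monitor, study-related adverse events with severity and a related/not-related attribution. The alternative box, covering all adverse events, is not selected. Clinical summaries are likewise limited to study-related SAEs and study-related unexpected events.

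Section 9.1 sets the incidence of treatment-emergent events over 8 weeks against the "known frequency of anakinra-related AEs in other populations". The first secondary endpoint makes the same comparison over 36 weeks. On procedures, 10.19 states that "CSF will be collected at Day 1, Week 36, and Week 44" in consenting, eligible participants. Section 15.2 lists "Headache, dizziness" and nausea among the known anakinra reactions.

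**The concern.** The causality code is the only attribution defined for every adverse event, serious or not. It should answer one question: is there a reasonable possibility that anakinra caused this? It does not, for two reasons. It adds procedures to the question, and it sets the bar at likely when 13.2 sets it at a reasonable possibility.

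Two uses are at stake. First, the study has a single independent Monitor and no DSMB, and the Monitor's event listing is built mainly on study-related events. A possible drug reaction that ends up as Unrelated may not appear there. Second, the comparison in 9.1 has a drug-attributed benchmark. To put a like quantity beside it, one needs a drug-attributed count from this trial, and most of those events will be non-serious ones for which 13.3 is the only attribution.

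**Working it through.** No formula tests this point. The check is to set the causality wording side by side.

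| Place | What is judged | Threshold |
|---|---|---|
| 13.3, Related | drug or procedures | likely |
| 13.3, Unrelated | drug or procedures | likely not |
| 13.3, SAEs after the study | treatment or participation | possibly |
| 13.2, suspected adverse reaction | drug | reasonable possibility |
| 13.2, UPIRTSO | drug | PI's opinion, no threshold |
| 13.5, initial SAE report | study treatment | none stated |
| 13.5, IRB and FDA triggers | study drug | related / associated, none stated |
| 9.1, Phase 1 count | any cause | not applicable |
| 9.1, Phase 1 benchmark | anakinra | as used in the outside sources |

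1. *An event that is possible but not likely.* It meets 13.2. It does not meet the Related code. Nor does it clearly meet the Unrelated code, which requires that a link be unlikely. It therefore has no defined place, and two assessors can code it differently.

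2. *Path to the Monitor.* If such an event is coded Unrelated, it is not study-related in the sense of Appendix A. It reaches the Monitor's report only if it falls under another selected box: routine illnesses and injuries, or the listed disease-related SAEs.

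3. *Drug versus procedure.* Treatment starts on Day 1 (10.21, 27.5), and an optional lumbar puncture with mild sedation may take place on the same day (10.19). A headache, dizziness or nausea that follows could come from either source. If judged likely due to either one, it receives the same code.

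4. *Benchmark.* The objective in 3.0 and the endpoint in 9.1 count treatment-emergent events without a causality condition, and the AE analysis in 12.2 uses no causality class. Only the outside frequency is restricted to anakinra-related events. Step 3 shows that the 13.3 code cannot turn the trial's count into a matching one.

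5. *Background rate.* Footnote f of the Schedule of Events records, before dosing, only SAEs tied to protocol-imposed interventions. Under that footnote the observational period gives no rate of ordinary events to subtract, so attribution is the main filter left.

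6. *Resolution.* With 20 subjects, one child is 1/20 = 5 percentage points. Section 12.3 considers proportions of 5% to 15%, that is 20 × 0.05 = 1 to 20 × 0.15 = 3 children. One child moved in or out of the drug-attributed group is therefore a visible change on the scale that the protocol itself uses. This is a unit of measurement, not an estimate of how often misattribution would occur.

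**The case against.** The strongest reply is that little depends on the 13.3 code. That is largely right, and it rules out three stronger readings.

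- A reader might infer that the code biases the primary safety count. It does not. The Phase 1 count takes every treatment-emergent event whatever its code, so an event called Unrelated is still counted and a lumbar-puncture event is counted either way.
- A reader might infer that drug-related SAEs cannot be identified for the IRB or FDA. The documents do not support that. All SAEs go to the sponsor within 24 hours without a causality condition, the initial report asks about study treatment specifically, the UPIRTSO judgement is the PI's and concerns the drug, and all deaths go to the IRB regardless of cause. What remains is that these judgements have no stated threshold and can disagree with the code on the CRF for the same event.
- A reader might infer that a possible but not likely event must be coded Unrelated. The wording leaves it without a clear code; it does not force that one.

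The Monitor also sees more than study-related events. Routine illnesses, with headache named, and listed disease-related SAEs are reported irrespective of attribution, and the Grade 3 and Grade 4 criteria in 13.4 use no causality code. This narrows the gap to possible reactions outside those groups but does not close it.

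Finally, the AE eCRF is not shown and may already separate drug from procedure. If so, the protocol text still needs to match it.

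**Conclusion.** The point holds as a conflict between rules. The 13.3 scale does not match the standard in 13.2, its own wording for post-study SAEs, or the drug-specific triggers in 13.5. For non-serious events it cannot separate anakinra from procedures, and it can leave a possible drug reaction out of the Monitor's listing. The mismatch in 9.1 is a separate fault: an all-cause count beside a drug-related benchmark, which the 13.3 code cannot repair.

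No size in events can be given. The protocol states neither the expected uptake of lumbar puncture nor any rate of procedure or background events, and uptake may be small because collection is optional and limited to children who need only mild sedation. The conclusion rests on the text alone, and on the assumption that the eCRF follows 13.3.

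**What to change.** 1. In 13.3 and the AE eCRF, replace the single code with two yes/no items: (a) is there a reasonable possibility that anakinra caused the event, and (b) is there a reasonable possibility that a study procedure caused it, naming the procedure. Align the post-study SAE sentence in 13.3 with the same standard.
2. In 13.2 and 13.5, state that item (a) is the drug-relatedness judgement for UPIRTSO, IRB and FDA reporting.
3. In Appendix A, define study-related as (a) or (b).
4. In 9.1, for the 8-week endpoint and the matching 36-week one, compare events with (a) = yes with the anakinra-related frequencies. Report all-cause treatment-emergent events beside them, without that benchmark.

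The cost is a few sentences and one extra eCRF field. Somewhat more events will be classed as possibly drug-related and reported. No visit, sample or clinical rule changes. Events already coded would need re-assessment on the two items.
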